 **H2.**
*IST increases the acceptance of strength training by older adults.*

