##### Exclusion Criteria

Inability to make autonomous decisions (e.g., inability to give valid informed consent) or to understand and consistently follow exercise instructions, due to significant cognitive impairment (assessed by Mini-Cog© and clinical judgement that precludes safe and autonomous participation) or other conditions that severely impair comprehension or communication.Presence of active, unstable or severe medical conditions that, in the judgement of the study’s doctor, restrict effective participation or significantly increase the risk of injury associated with the programme, including, but not limited to:○Cardiovascular: Conditions leading to exclusion include uncontrolled arterial hypertension, defined as a resting Systolic Blood Pressure (SBP) > 180 mmHg or a resting Diastolic Blood Pressure (DBP) > 110 mmHg. Other exclusion criteria are a recent major cardiovascular event (within the last 6 months), such as unstable angina, myocardial infarction or cardiac surgery; decompensated congestive heart failure (New York Heart Association [NYHA] Class III–IV); uncontrolled, clinically significant ventricular arrhythmias; or symptomatic severe aortic stenosis.○Neuromuscular: Advanced or rapidly progressive degenerative neuromuscular diseases (e.g., Amyotrophic Lateral Sclerosis [ALS]) that preclude safe and effective exercise performance or could be exacerbated by IST.○Musculoskeletal: Active/severe multi-joint inflammatory arthritis, recent unconsolidated fractures in involved areas, major orthopaedic surgery < 6 months that contraindicates exertion, or severe chronic musculoskeletal pain significantly exacerbated by IST despite adjustments.○Respiratory: Severe Chronic Obstructive Pulmonary Disease (COPD), defined as stage III-IV according to the Global Initiative for Chronic Obstructive Lung Disease (GOLD) guidelines, with significant limiting symptoms, or severe, poorly controlled asthma.○Other severe or unstable medical conditions: Exclusion criteria also include advanced Chronic Kidney Disease (CKD), such as patients on dialysis or those with an estimated Glomerular Filtration Rate (GFR) < 30 mL/min/1.73 m^2^ without explicit approval from their nephrologist; uncontrolled diabetes mellitus with severe acute or chronic complications (e.g., untreated proliferative retinopathy, severe peripheral neuropathy with risk of ulceration); or any other pathology deemed an absolute contraindication to participation by the study’s doctor.Inability to commit to attending at least 90% of the scheduled training sessions during the 16 weeks of the study.

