#### 2.2.2. Pre-Intervention Assessment

One week before starting the 16-week IST, a comprehensive baseline assessment will be performed on the selected subjects to collect baseline data. This assessment, conducted by a physical activity professional and the research group doctor, will allow for detailed monitoring and accurate assessment of the effects of the programme, including the following variables:Physiological Variables: BP and heart rate HR (Omron M3 Comfort^®^ blood pressure monitor, HEM-7134-E, Omron Healthcare Co., Kyoto, Japan) and O2 saturation (OXYM4000 pulse oximeter, Quirumed S.L.U., Valencia, Spain) will be measured. Three resting measurements will be taken per participant, using the mean as the final data.Functional Capacity:○MVIC: The MVIC of each muscle group of the IST programme will be assessed at individualised intermediate angles (determined according to anatomical structure and motor restrictions, recorded with a HALO© digital goniometer). The CIEX SYSTEM machine (Ciex Systems©, Durango, Spain) with sensors and Chronojump software (Chronojump Boscosystems^®^, Barcelona, Spain) will be used for instantaneous measurement and visualisation of strength, tools also used in all IST sessions and for monitoring purposes.○Static Posture Assessment: Participants will be photographed in anatomical position (frontal and sagittal planes) with a Casio Exilim Pro EX-F1 camera (configuration: level tripod, lens at umbilical height, at 4 m, optical zoom, aperture priority, focal length 50 mm, f5.6, ISO 200) [81]. An analysis of documented validity and reliability for postural analysis will be performed with Kinovea^®^ software (v.0.9.x+) [82,83]. Adhesive markers or direct image identification may be used for key anatomical points [84] (sagittal: tragus, C7, acromion, greater trochanter, lateral femoral epicondyle, peroneal malleolus; frontal: acromions, anterior superior iliac spine (ASIS), posterior superior iliac spine (PSIS), patellar centre, tibial malleoli). Postural parameters will be calculated from these points (sagittal: head-neck alignment (HNA) [82], shoulder alignment, estimated spinal curvatures, pelvic tilt [84], knee alignment; frontal: head tilt/symmetry, shoulder height, pelvic symmetry [81], lower limb alignment [82]). Angles (degrees) and distances (cm/mm, after calibration if size reference is used) shall be recorded. Pre-post change will be an outcome of interest. Image analysis shall be performed, if possible, by a blinded assessor (see Section 2.1.3) [83].HRQoL: The EuroQol EQ-5D-5L questionnaire (5 items, 5 dimensions, 5 response levels) will be used [85,86]. This instrument includes two parts: a descriptive system comprising five dimensions (mobility, self-care, usual activities, pain/discomfort, anxiety/depression), each with five response levels, and a VAS where participants rate their overall health.Applicability of the IST Protocol (scales administered post-intervention):○Safety (H1): Assessed by: (1) Analysis of Adverse Events (AEs) (incidence, type, severity, relationship to IST) over 16 weeks (procedures detailed in Section 2.4.3); ‘low risk’ if the incidence of IST injuries is minimal. (2) Perceived Safety: 5-point Likert scale (1 = extremely unsafe, 5 = extremely safe) post-programme, with face validity and based on similar approaches [87]; a mean score ≥ 4 will be expected.○Acceptability (H2): Assessed by compliance rates (≥90% sessions) and overall satisfaction (5-point Likert scale: 1 = extremely dissatisfied, 5 = extremely satisfied) post-programme, using validated measures [88]; a mean satisfaction score ≥ 4 will be expected.○Difficulty (H3): Assessed with a 5-point Likert scale on perceived challenge (1 = not challenging at all, 5 = extremely challenging) post-programme, validated approach [89]; a mean score ≤ 2 will be expected.Genetic Analysis: Saliva samples will be collected using buccal swabs (4N6FLOQSwab, Life Technologies, Waltham, MA, USA). DNA will be extracted from these samples (QIAmp DNA Mini kit, Qiagen, Venlo, The Netherlands) and subsequently quantified (Qubit, Life Technologies). Genetic polymorphisms, specifically Single Nucleotide Polymorphisms (SNPs) and Insertions/Deletions (INDELs), will be analysed in genes associated with the response to strength training, hypertrophy, and strength gains [63,64,65,66,67,68,69,71,72,73]. Specifically, genes linked to the following will be analysed:○Muscle fibre typology: such as ACTN3 (R variant associated with a higher proportion of type II fibres, crucial for strength/power and affected by sarcopenia/dynapenia in ageing) [63,64].○Response to training: including ACE [63,65,66], NRF2, CKMM, MCT1, AMPD1, and the co-activators PPARGC1A and PPARGC1B (involved in mitochondrial biogenesis and exercise adaptation).○Muscle fibre damage and regeneration: genes such as IGF2, MLCK, CASP [72], MMP3 [72], TNC and GDF5 [73], which influence the response to exercise microtrauma and its repair. Moderate exercise-induced muscle damage (EIMD), potentially triggered by IST at long angles, is considered to contribute to remodelling and adaptation.○Vascularisation: NOS3 and VEGFA [67,69], essential for oxygen/nutrient supply, muscle growth and recovery, optimising metabolic stress and hypertrophic response.○Inflammation: TNF-α, CRP [60], IL-6 [60] and IL6-R, which are relevant because inflammation contributes to sarcopenia and modulates the anabolic response [70].○Oxidative damage response capacity: SOD2 [71], CAT and GPX, crucial for muscle recovery and adaptation to training stress.○Fat and carbohydrate metabolism (nutrigenomic factors): Polymorphisms in FABP2, ADRB2, ADRB3, FAT/CD36, UCP2, GCKR, ADCY5 and GIPR, which may influence nutrient uptake and hypertrophic response [74,75,76].

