#### 2.3.2. Analysis Strategy

Primary and secondary quantitative variables will be compared pre-post with Student’s *t*-tests for related samples, after testing for normality (Shapiro-Wilk). If the data are not normally distributed or contain outliers, non-parametric tests (e.g., the Wilcoxon signed-rank test) will be employed. Effect sizes (Cohen’s d) and confidence intervals will be calculated. Multivariate analyses will include a multiple linear regression to explore the influence of genetic and environmental variables on strength and muscle mass improvement, with Bonferroni correction for genetic analyses. Qualitative variables (e.g., sarcopenia diagnosis) will be analysed by using McNemar tests. Applicability variables (Likert scales, adverse events) will be analysed with descriptive statistics and *t*-tests or Wilcoxon tests for pre-post comparisons on Likert scales. Additionally, exploratory subgroup analyses will be performed to assess whether the response to IST on primary variables differs according to sex, age ranges (70–79 vs. ≥80 years) and baseline severity of sarcopenia/dynapenia. Adjustment for baseline covariates will be considered in regression models. The software will be IBM SPSS v29.0 and R v4.3.1.

For the assessment of the secondary hypotheses concerning the applicability (Section 2.2.2) of the IST protocol, specific analyses will be carried out:

Hypothesis H1 (low injury risk): This will be assessed through two approaches. First, Adverse Events (AEs) will be recorded (including their type, severity, and causality), and ‘low risk’ will be inferred if the incidence of IST-related injuries is minimal and comparable to or lower than rates reported in the literature for strength training in older adults [1,33,34,35]. Second, Perceived Safety will be measured post-intervention using a 5-point Likert scale; the approach for this subjective scale is based on similar methods used in previous research [87]. The hypothesis will be supported by a mean score of ≥4.

Hypothesis H2 (high acceptance): This will be assessed by: (1) compliance rate, with a success threshold of ≥90% of completed sessions, and (2) a satisfaction score from a 5-point Likert scale administered post-intervention, using a validated measurement approach [88]. The hypothesis will be supported by a mean satisfaction score of ≥4.

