Hypothesis H3 (low perceived difficulty): This will be assessed using a 5-point Likert scale for perceived technical difficulty post-intervention, based on validated methods [89]. The hypothesis will be supported by a mean score of ≤2.

Hypothesis H4 (Genetic influence). The association between polymorphisms (muscle typology [63,64], inflammation [70,71], tissue regeneration [72,73], energy metabolism [74,75,76]) and improvements in mass/strength (IST) will be analysed by multiple linear regression, adjusting for covariates and with the Bonferroni correction test.

For the Likert-based outcomes (H1–H3), the magnitude of change will also be assessed by calculating Cohen’s d.

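### Section 2.3.2 plans pre-post tests and a Cohen's d of change on Likert scales that are given only at week 17, so these parts of the H1–H3 analysis cannot be run

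*Protocol article*

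**What the plan says.** Section 2.3.2 of the protocol article says that the applicability variables will be analysed descriptively and with t-tests or "Wilcoxon tests for pre-post comparisons on Likert scales". It closes with a sentence on the Likert outcomes of H1–H3: "the magnitude of change will also be assessed by calculating" Cohen's d.

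Section 2.2.2 introduces the same scales as "Applicability of the IST Protocol (scales administered post-intervention". Section 2.2.1 gives each of them a single time point, week 17, and names the post-intervention mean as the metric.

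The rules for the three hypotheses are:

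- **H1 (low injury risk).** Low risk "will be inferred if the incidence of IST-related injuries is minimal and comparable to or lower than rates reported in the literature", together with a mean perceived safety of at least 4.
- **H2.** The Introduction words it as "IST increases the acceptance of strength training by older adults". Section 2.3.2 labels it high acceptance and asks for at least 90% of sessions completed and mean satisfaction of at least 4. The exclusion criteria include "Inability to commit to attending at least 90% of the scheduled training sessions".
- **H3 (technical simplicity).** Mean difficulty of at most 2. Section 2.2.2 describes the item as a "5-point Likert scale on perceived challenge (1 = not challenging at all, 5 = extremely challenging"; Section 2.3.2 describes it as a "5-point Likert scale for perceived technical difficulty post-intervention".

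For adverse events, the outcome definition in Section 2.2.1 covers weeks 1–16, whereas Section 2.4.3 has active safety monitoring running for the whole study.

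**The concern.** A paired test and an effect size of change both need two scores per person, and these scales yield one. Whoever runs the analysis must either drop a stated analysis without notice or invent a reference value. Both would be departures from the plan on an aim that stands in the trial's title.

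Three smaller mismatches sit beside this one. H2 claims an increase, with no baseline and no comparator to show it. The H3 item, as Section 2.2.2 describes it, can measure effort where the hypothesis is about technique. The adverse-event outcome can be read as leaving out maximal strength tests that the protocol itself schedules.

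**Working it through.** **1. When the scales are given.**

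| Place in the protocol article | Content |
|---|---|
| Table 1, baseline row | No applicability scale listed |
| Table 1, final evaluation row | Applicability questionnaires listed |
| Section 2.2.1, opening | Default of weeks 0 and 17, unless an item states otherwise |
| Section 2.2.1, applicability items | Week 17 only; metric is the post-intervention mean |
| Section 2.2.2 | Scales given after the intervention |
| Section 2.2.3 | Questionnaires added at the final visit |
| Section 2.3.2 | Pre-post tests and Cohen's d of change |

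The default in Section 2.2.1 does not supply a week-0 score, because the applicability items do state otherwise. No other Likert outcome is described to which the pre-post wording could refer. The first member of each pair is missing.

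**2. The number of participants.** The protocol gives no calculation for H1–H3; its only one is for knee extensor strength. That one reproduces: for a two-sided paired t-test with d = 0.80 and α = 0.05, power is 0.790 at n = 14 and 0.821 at n = 15, so N = 15. Allowing 15% losses, 15/0.85 = 17.6, so 18. I use n = 15 and n = 18 below.

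**3. Precision of the threshold rules.** The half-width of a 95% CI for a mean is t(0.975, n−1) × SD/√n. The protocol gives no SD for these scales, so 0.8 is an assumption, with a range of 0.6 to 1.0.

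- n = 15, SD 0.8: 2.145 × 0.8/√15 = 0.44 (range 0.33 to 0.55)
- n = 18, SD 0.8: 2.110 × 0.8/√18 = 0.40 (range 0.30 to 0.50)

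An observed mean of exactly 4.0 with n = 15 would therefore carry an interval of about 3.56 to 4.44. If the true mean were 3.8, the rule of at least 4 would still be met with probability 1 − Φ((4 − 3.8)/(0.8/√15)) = 1 − Φ(0.97) = 0.17 (0.10 to 0.22 over the SD range).

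**4. H2 adherence.** Two sessions a week for 16 weeks is 32 sessions, and 0.9 × 32 = 28.8, so 29 must be completed (29/32 = 90.6%; 28/32 = 87.5%). The same 90% appears as a commitment required at entry (Exclusion Criteria), as a criterion for discontinuation even after the period has been extended (Section 2.1.2), and as the success threshold (Section 2.3.2). Section 2.1.2 also allows up to four extra weeks after two or more consecutive excused absences. The outcome is partly met by selection, and its value depends on whether discontinued participants stay in the denominator.

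**5. H3 item.** Every contraction ends in a phase at 100% maximal effort (Section 2.1.2, Table 2). Someone who finds the technique easy and the effort hard could rate the challenge high, and H3 would then fail for a reason unrelated to technique.

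**6. H1 injuries.** The outcome window is weeks 1–16 (Section 2.2.1; Section 2.2.2 also speaks of 16 weeks). Maximal strength tests fall in weeks 0 and 17, and an extension can run beyond week 16. With no injuries observed, the exact 95% two-sided upper limit is 1 − 0.025^(1/n):

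- n = 18: 1 − 0.025^(1/18) = 18.5%
- n = 15: 1 − 0.025^(1/15) = 21.8%

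**The case against.** The strongest reply is that the pre-post test decides nothing. Section 2.2.1 fixes the metric as the post-intervention mean, and the rules in Section 2.3.2 for the Likert scales use thresholds on that mean alone. Deleting one clause and one sentence leaves every hypothesis decision as it was. This stands. A reader might infer that H1–H3 cannot be assessed at all; the documents do not support that. The thresholds, adverse-event counts and adherence can all be computed.

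Other replies also stand in part:

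- **Adherence.** A reader might infer that the 90% criterion is met by construction. It is not. A commitment at entry is not attendance, data from those who stop are kept, and Section 2.3 plans an intention-to-treat analysis with attendance of at least 90% defining only the per-protocol set. Selection is partial.
- **Injury risk.** A reader might infer that a finding of low risk is almost guaranteed. No calculation shows this, because the required incidence has no number and is also to be compared with published rates. With an assumed true risk of 10% per participant, no injury would be seen only 0.9^18 = 15% of the time (0.9^15 = 21% with 15). A numeric benchmark may be left to an analysis plan, so its absence is not counted here.
- **Adverse events.** A reader might infer that events outside weeks 1–16 go unrecorded. Section 2.4.3 asks about symptoms at every training session and records all events. What remains is an outcome window narrower than the collection rule.
- **Remedies partly present.** Section 2.3.2 already mentions confidence intervals for secondary quantitative variables, and already labels H2 as high acceptance. Section 2.1.3 encourages those who stop to attend week 17. The H3 item's actual text is not shown, so the mismatch lies in its description and anchors.

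None of this provides a week-0 score.

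**Conclusion.** The contradiction is firm and needs no assumption: the pre-post tests and the d of change on the H1–H3 scales cannot be run. Its effect is limited, because the threshold rules remain workable. Those rules judge a point estimate and ignore a half-width of about 0.4 scale points, a figure that rests on an assumed SD of 0.8.

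The accompanying points are smaller but real. H2's claimed increase cannot be shown. The adherence threshold is partly selected for. The H3 item as described does not match its hypothesis. The two adverse-event windows disagree, and even no injuries among 18 would be compatible with a risk of up to 18.5% per participant.

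These are secondary outcomes of an exploratory single-arm trial and the primary outcomes are unaffected, so the point should be fixed but does not endanger the trial's main analysis.

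**What to change.** In Section 2.3.2, delete the pre-post tests and the Cohen's d of change for the Likert scales. Report each week-17 mean with its 95% CI against its threshold (4, 4 and 2). In the same edit:

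1. **H2.** Restate it in the Introduction as high acceptance, matching Section 2.3.2. Compute adherence over the 32 scheduled sessions for everyone who starts, including those discontinued.
2. **H3.** Make the item ask about technical difficulty, separately from effort, and use the same description in Sections 2.2.2 and 2.3.2.
3. **H1.** Reconcile the outcome window in Sections 2.2.1 and 2.2.2 with Section 2.4.3, so that the strength tests in weeks 0 and 17 and any extension weeks are counted. Give an exact CI with the injury count.

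The cost is a few sentences and one reworded item. Sections 6.1 and 7.1 describe registration and ethics approval as still to come, so the protocol's own timetable leaves room for the change before recruitment. The price is that the statements on H1 and H2 become more modest.

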Stimulation of type II fibres is crucial, but requires high intensities of effort [27,28,29,30]. Traditional resistance training (TRT), while effective when following recommended guidelines (2–3 sets of 6–12 repetitions at 70–85% of 1 RM, performed 2–3 times per week) [1] and incorporating proposed power exercises (using moderate loads at high speeds, typically 40–60% of 1 RM), presents certain challenges: high-threshold motor units are only activated near muscular failure [31,32], which increases the risk of compensatory movements and potential injuries [1]. In addition, high-speed, moderate-load exercises require high technical control and may injure various joints [33,34,35].

In this context, isometric strength training (IST) is a valuable alternative, used in rehabilitation, physical training and special populations [36,37,38,39]. Maximal voluntary isometric contraction (MVIC) is a reliable measure of health and sports performance [39,40,41]. IST has been shown to be effective against sarcopenia and dynapenia, inducing improvements in strength and hypertrophy [42,43,44,45]. Movement intention can be as effective as contraction velocity in improving Rate of Force Development (RFD) [39,46], and mechanical strain at maximal IST can exceed that of maximal concentric actions [36,47], optimising stimulation of high-threshold fibres.

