1.Other Indicators of Sarcopenia and Dynapenia:○Handgrip Strength: Specific measurement variable: Maximal handgrip strength, measured in kilograms (kg) (Jamar Dynamometer). Analysis metric: Absolute change from baseline to week 17. Method of aggregation: Mean and SD. Time point(s): Baseline (week 0) and post-intervention (week 17). Clinical Relevance: A component of the sarcopenia diagnosis and a predictor of functionality and mortality.○Gait Speed: Specific measurement variable: Usual gait speed over a 4 m course, measured in meters/second (m/s) (Newtest Powertimer). Analysis metric: Absolute change from baseline to week 17. Method of aggregation: Mean and SD. Time point(s): Baseline (week 0) and post-intervention (week 17). Clinical Relevance: A measure of physical performance, a component of the sarcopenia diagnosis, and a predictor of adverse outcomes.○MVIC of other muscle groups: Specific measurement variable: MVIC for the peck deck, pull over, lateral shoulder elevation, leg curl, low back, hip abduction and hip adduction, measured in Newtons (N) (CIEX SYSTEM). Analysis metric: Absolute change from baseline to week 17. Method of aggregation: Mean and SD of the change per exercise. Time point(s): Baseline (week 0) and post-intervention (week 17). Clinical Relevance: Assesses the training response across different body regions.○Sarcopenia Status: Specific measurement variable: Diagnostic status of sarcopenia according to EWGSOP2 criteria (based on muscle strength, muscle mass, and physical performance). Analysis metric: Change in the proportion of participants meeting the diagnostic criteria from baseline to week 17. Method of aggregation: Frequencies and percentages. Time point(s): Baseline (week 0) and post-intervention (week 17). Clinical Relevance: Quantifies the overall impact of the intervention on the diagnostic status of the condition.2.Health-Related Quality of Life (HRQoL):○Specific measurement variable: The index score derived from the EQ-5D-5L descriptive system and the Visual Analogue Scale (VAS) score of the same questionnaire. Analysis metric: absolute change from baseline to week 17 for both the index score and the VAS score. Method of aggregation: Mean and SD of the changes. Time point(s): Baseline (week 0) and post-intervention (week 17). Clinical Relevance: Measures the overall self-perceived health and the impact of the intervention on multiple dimensions of participant well-being.3.Applicability of the IST Protocol:○Perceived Safety: Specific measurement variable: Score on a 5-point Likert scale for perceived safety. Analysis metric: Mean score post-intervention. Method of aggregation: Mean and SD. Time point(s): Post-intervention (week 17). Relevance: Assesses the participant’s subjective perception of safety, providing data to test hypothesis H1.○Acceptance/Satisfaction: Specific measurement variable: (1) Adherence rate (% of completed sessions); (2) Score on a 5-point Likert scale for overall satisfaction. Analysis metric: Percentage for adherence; Mean score post-intervention for satisfaction. Method of aggregation: Percentage for adherence; Mean and SD for satisfaction score. Time point(s): Adherence monitored continuously during the intervention (weeks 1–16); Satisfaction assessed post-intervention (week 17). Relevance: Measures the feasibility and appeal of the intervention to participants, providing data to test hypothesis H2.○Perceived Difficulty: Specific measurement variable: Score on a 5-point Likert scale for perceived difficulty. Analysis metric: Mean score post-intervention. Method of aggregation: Mean and SD. Time point(s): Post-intervention (week 17). Relevance: Evaluates the perception of technical simplicity, providing data to test hypothesis H3.○Adverse events: Specific measurement variable: Incidence, type, severity and causality (relationship to IST). Analysis metric: Frequencies and descriptive summary. Method of aggregation: Counts and percentages. Time point(s): Monitored continuously during the intervention period (weeks 1–16). Relevance: Assesses the objective safety profile of the protocol, providing data to test hypothesis H1.

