## 3. Discussion

The present 16-week IST protocol aims to evaluate its effect on sarcopenia, dynapenia, quality of life and applicability in adults aged 70 years and above, while also analysing the influence of genetic and environmental variables on the variability of the response.

Programmed strength training is the best strategy to combat sarcopenia and dynapenia [1,5,16,17]. To stimulate type II fibres, protocols have evolved towards dynamic explosive actions with light loads and lifting high loads to muscle failure [1]. However, these TRT methodologies require high technical proficiency and effort, making them difficult to apply in older adults due to physical and psychological limitations. The need to execute complex dynamic movements can be intimidating or painful for older adults with comorbidities (osteoarthritis, chronic pain, reduced mobility) and psychological barriers (fear of falling, low self-efficacy, perception of gymnasiums). Lack of mobility and difficulty maintaining technique with high loads or ballistic movements increase the risk of injury [1], underlining the need for more suitable alternatives.

IST, due to its biomechanical characteristics, could be an effective and safe option. It is not technically difficult, does not require movement and allows angles to be adjusted to individual needs, overcoming barriers such as apprehension of complex movements or pain induced by them. This facilitates concentration of effort, favouring a more accessible activation of high-threshold fibres. Static and controlled maximal effort can be safer and psychologically more approachable.

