The benefits of this IST protocol on strength and muscle mass are expected to be due to combined neuromuscular mechanisms. Neurally, 100% ME seeks to maximise the activation and firing rate of high-threshold motor units, following Henneman’s principle [32]. Muscularly, the mechanical strain of long, high-intensity isometric contractions is a potent stimulus for protein synthesis and hypertrophy [42,43,44,45]. Gradual progression of intensity and duration will facilitate these adaptations. Metabolic stress from vascular occlusion may contribute to this, and the choice of intermediate angles, in addition to safety, aims to optimise the generation of active tension by favouring a greater number of actin-myosin cross-bridges.

Several studies have shown that IST can significantly increase muscle strength and hypertrophy [42,43,44,45], positioning it as an effective tool, possibly more so than TRT, to combat sarcopenia and dynapenia in the elderly.

Beyond the technical complexity, TRT with explosive execution and high loads increases the risk of injury [33,34,35]. In contrast, IST is used in rehabilitation and special populations [36,37,38,39] because it allows safe strength work with minimal or no pain in specific ranges [36,37]. This is a practical advantage for older people with joint pain, as strengthening without exacerbating pain improves viability and can have acute analgesic effects [57,58], improving quality of life. The lower likelihood of severe DOMS and lower perceived technical difficulty may also favour acceptance of and adherence to IST.

One consideration in high-intensity IST is an acute BP response. Although maximal isometric contractions may transiently elevate BP [80,91], our protocol seeks to mitigate this risk by including participants with controlled hypertension, gradual progression of intensity, instruction for continuous breathing (avoiding prolonged Valsalva) [78,79], and constant monitoring.

Therefore, IST could be considered a safer and more effective alternative to TRT in older adults to improve their quality of life.

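### H1 infers low injury risk from a point incidence with no numerical threshold and no allowance for uncertainty, and 18 participants cannot support that inference

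*Protocol article*

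**What the plan says.** H1 is a secondary hypothesis: isometric strength training (IST) carries a low risk of injury in older adults. It has an objective part (adverse events) and a subjective part (perceived safety).

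The objective part is worded in two ways:

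- Section 2.3.2 (Analysis Strategy): low risk "will be inferred if the incidence of IST-related injuries is minimal and comparable to or lower than rates reported in the literature". The comparator in full is an incidence "comparable to or lower than rates reported in the literature for strength training in older adults [1,33,34,35", so references 1, 33, 34 and 35 are the source of those rates.
- Section 2.2.2 (Pre-Intervention Assessment): low risk "if the incidence of IST injuries is minimal", with no literature comparator.

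For the perceived-safety scale, Section 2.3.2 says "The hypothesis will be supported by a mean score of ≥4".

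Section 2.2.1 sets out the adverse-event analysis as follows: "Analysis metric: Frequencies and descriptive summary. Method of aggregation: Counts and percentages". No interval is planned for the injury incidence.

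References 33 to 35 also appear in the Introduction, for the statement that "high-speed, moderate-load exercises require high technical control and may injure various joints [33,34,35", and in the Discussion, for the statement that "TRT with explosive execution and high loads increases the risk of injury [33,34,35". Reference 1 is cited in the Discussion where "difficulty maintaining technique with high loads or ballistic movements increase the risk of injury [1", but the Introduction also cites it for general resistance-training guidelines.

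**The concern.** The rule turns an observed count into a conclusion. Both of its conditions lack a number: *minimal* is undefined, and the literature rate has no value, denominator (person, session or hour) or margin for *comparable*. Whether the rule is met can therefore be settled after the injuries have been counted. The two sections also disagree on whether a comparator is needed at all.

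The choice of sources adds a doubt. H1 uses references 33 to 35 as a benchmark for strength training in older adults, while the protocol's own argument uses them to show that some forms of training injure people.

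The larger problem is precision. The rule looks only at the point incidence. In a sample this small, few or no injuries is a likely result even when the risk is far from low. At stake is a safety conclusion that readers would carry into the protocol's foreseen uses in geriatric rehabilitation and primary care. The limitations in Section 4 do not mention how imprecise the injury estimate will be.

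**Working it through.** **Inputs from the protocol**

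- 15 evaluable and 18 recruited, with 15% losses (Section 2.3.1).
- Two 30-minute sessions a week for 16 weeks, so 32 sessions per person (Abstract and Table 1).
- Injury rate in the literature: not given. Values of 2% to 20% of participants are assumed below, only to show how the rule behaves.

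**1. The plan's own figure.** The sample size was set on quadriceps strength. For a paired t-test with d = 0.80 and two-sided 5%, the noncentral t distribution gives 79.0% power at n = 14 and 82.1% at n = 15. So 15 are needed, and 15 / 0.85 = 17.65, rounded up to 18. The stated 15 and 18 reproduce. No figure is stated for H1.

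**2. What zero injuries would show.** With 0 events in n people, the exact two-sided 95% upper limit is 1 − 0.025^(1/n).

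- n = 18: 1 − 0.025^(1/18) = 18.5% (one-sided: 1 − 0.05^(1/18) = 15.3%).
- n = 15: 1 − 0.025^(1/15) = 21.8% (one-sided 18.1%).

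With 1 injury in 18 (5.6%), the exact 95% interval is 0.1% to 27.3%.

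**3. How often zero injuries would occur.** The probability is (1 − p)^18.

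| True risk p | P(0 of 18) |
|---|---|
| 2% | 69.5% |
| 5% | 39.7% |
| 10% | 15.0% |
| 15% | 5.4% |

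**4. Per training hour.** Full attendance gives 18 × 32 × 0.5 h = 288 h. With zero injuries the upper 95% limit is −ln(0.025) / 288 × 1000 = 12.8 per 1000 h. If only 15 people contribute, exposure is 15 × 32 × 0.5 = 240 h and the limit is 3.689 / 240 × 1000 = 15.4 per 1000 h.

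**5. Could any result establish a rate below a comparator?** At one-sided 5%, zero events exclude a rate p0 only if (1 − p0)^n ≤ 0.05, that is n ≥ ln(0.05) / ln(1 − p0).

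| Assumed comparator p0 | Injury-free participants needed |
|---|---|
| 2% | 149 |
| 5% | 59 |
| 10% | 29 |
| 15% | 19 |
| 20% | 14 |

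With 18 people, no result excludes 15% or less. At 20%, 0 of 18 is required, and this happens with probability 0.90^18 = 15% if the true rate is half the comparator.

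**6. The comparator read as observed rate at or below literature rate.** The undefined *minimal* condition is set aside here.

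| Assumed comparator | Injuries allowed of 18 | Passes if true rate equals comparator | Passes if true rate is twice comparator |
|---|---|---|---|
| 2% | 0 | 69.5% | 48.0% |
| 5% | 0 | 39.7% | 15.0% |
| 10% | 1 | 45.0% | 9.9% |
| 20% | 3 | 50.1% | 3.3% |

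The pass rate at twice the comparator is high only when the comparator is low, which is where a claim of low risk would matter most.

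**The case against.** The strongest defence has five parts.

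- **The rule has two conditions.** A reader might infer that an injury rate merely similar to that of risky training would count as low risk, so that the safety claim rests on the comparator. The text does not support this. Section 2.3.2 also requires the incidence to be minimal, Section 2.2.2 uses no comparator, and perceived safety is assessed separately. This stands. But an undefined condition gives no fixed protection, and a perception score does not estimate an injury rate.
- **Leniency is not shown.** A reader might call the comparator lenient. The documents show only where references 33 to 35 are cited, not what rates they report. They may contain conventional-training rates, which may be low, and reference 1 is also cited for general guidelines. This stands: the sources look mismatched on the protocol's own use of them, and no more can be said.
- **H1 is secondary and makes no claim against traditional training.** This stands. The statements that IST is safer belong to the Discussion and Conclusions and are not outputs of the H1 rule. The study also calls itself exploratory and plans adverse events as counts. Counting is appropriate; the fault lies in inferring low risk from the counts.
- **Not every low count passes.** A reader might say that zero or one injury would meet almost any benchmark. That is too strong: 1 of 18 is 5.6%, or 1 / 288 × 1000 = 3.5 per 1000 h at full attendance, and fails any lower benchmark.
- **The number could sit in an analysis plan.** A benchmark value or interval method could. But the article itself fixes this inference rule, words it in two ways, and gives numerical thresholds for the other applicability criteria (perceived safety and satisfaction at least 4, attendance at least 90%, difficulty at most 2).

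**Conclusion.** The point holds as follows. The injury part of H1 infers low risk from a point incidence, against an undefined standard and unstated literature rates, and Sections 2.2.2 and 2.3.2 give different rules. Even the best possible result, no injuries among 18, leaves risks up to 18.5% compatible with the data (21.8% with 15 evaluable). That result would be seen in 15% of such trials at a true risk of 10% and in 40% at 5%. The rule can therefore report low risk when the data cannot support it.

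The participant-level limits need only the sample size and independence between participants. The hourly limits also assume full attendance and a constant rate. The comparator calculations rest on assumed rates, because the protocol gives none. The documents do not show that the comparator is lenient or that H1 claims superiority to traditional training. The primary outcomes are not affected.

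**What to change.** Before recruitment:

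1. Reconcile Sections 2.2.2 and 2.3.2 so that H1 has one injury criterion.
2. Report IST-related injuries per participant and per 1000 training hours actually delivered, each with an exact 95% confidence interval.
3. Replace the rule that infers low risk with a descriptive conclusion that quotes the upper limit.
4. Make no statement of comparability with other strength training unless that limit lies below a numerical benchmark, with its denominator, written into the protocol beforehand.

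The fourth condition will rarely be met. With 18 participants and no injuries, it needs a benchmark above 18.5% per participant, or above 12.8 per 1000 h at full attendance. In practice the descriptive conclusion is the workable route.

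The change is to wording and reporting: no added visits or participants, and attendance is already recorded. The cost is that the injury part of H1 will probably be reported descriptively and not as supported.
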